**Methods:**

A prospective, multicenter, open-label, controlled, parallel, phase IV clinical trial of 402 smoker patients prepared to quit smoking. The study was conducted in 10 hospitals in Spain. A control group is compared to 2 intervention groups in which the duration of the drug is increased without increasing its dose, administering half and all, respectively, of an additional marketed container that includes 100 tablets. Thus, participants will be randomized to three groups in a 1:1:1 ratio to receive cytisinicline: (1) a control group treated with cytisinicline according to the usual clinical guidelines and product information (25 days); (2) a group with a 50-day cytisinicline regimen (an additional 25 days at a dose of 1.5 mg every 12 hours), seeking to increase its efficacy while minimally impacting adherence; and (3) a group with a 75-day regimen (an additional 50 days at a dose of 1.5 mg every 12 hours), attempting to increase its efficacy, although the longer duration of the drug may threaten adherence. Efficacy in the 3 arms will be analyzed through sustained abstinence at 6 and 12 months, point abstinence rate assessed every 7 days, and abstinence rate from Day 25 to Day 50 and from Day 25 to Day 75 in the 3 study arms. (1) The variation in withdrawal and craving symptoms in the 3 groups, (2) safety through the percentage of adverse events in the 3 treatment arms, and (3) economic impact by evaluating the cost-effectiveness and cost-utility ratios of the 2 prolonged regimens versus the usual clinical cytisinicline regimen. To calculate the differences between the 3 groups for each outcome variable, a univariate analysis will be performed. Statistically significant variables will be included in a multivariate model.

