### Statistical Analysis

#### Sample Size Determination

Based on clinical experience, it is estimated that the efficacy of cytisinicline prescribed in accordance with the data sheet is 30% (*P*^1^=.30), and that this efficacy will be greater if the maintenance regimen is extended over time. In this sense, it is hypothesized that the intermediate maintenance regimen could achieve an efficacy of 45% (*P*^2^=.40) and with the longest regimen, 50% sustained abstinence could be achieved (*P*^3^=.50). To obtain 80% power (pow=0.80) to detect differences at a 5% significance level (α=.05), 110 patients would need to be included in each arm. A loss rate of 21% is assumed, giving a final sample size of 402 patients (N=402).

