### Efficacy Analysis

To determine the main objective of the work, the efficacy variable will be constructed as a dichotomous variable, resulting from an algorithm that will be constructed for this purpose once all the data from the study have been obtained. To study the causality between efficacy and treatment prolongation, a multivariate logistic regression will be constructed. To determine candidate variables, candidate variables will first be tested in a univariate regression. Those variables whose statistical significance has a *P* value of <.20 will become part of a multivariate model. The model that best explains causality will be determined using a measure of relative statistical model quality, the Akaike information criterion. The risk measure to be calculated is the relative risk with its 95% CI. Interim follow-up assessments will be analyzed using a survival analysis to determine the duration of abstinence after the smoking cessation date.

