### Safety Analysis

The frequency and percentage of occurrence of adverse reactions shall be determined and categorized according to type/intensity. Calculate whether there are differences in each group compared to what is expected according to the product label.

To examine differences in the data between groups defined by the presence/absence of adverse events, the chi-square test will be applied for qualitative variables and the *t* test or the Mann-Whitney *U* test for quantitative variables. Finally, the causal relationship between safety, defined by the absence of adverse events, and treatment prolongation will be verified using multivariate logistic regression. To determine candidate variables, those with a statistical significance of *P*<.20 will be tested and included in a multivariate model.

All analyses will be performed with the statistical package SPSS (version 19.0; IBM Corp), and statistically significant values will be considered those whose *P* value is <.05.

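### The main efficacy model is selected from the outcome data, retention of treatment arm is not stated, and logistic regression is paired with a relative risk without a method that yields one

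*Protocol article*

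**What the plan says.** The Efficacy Analysis section of the protocol article deals with the main objective directly: "To determine the main objective of the work, the efficacy variable will be constructed as a dichotomous variable". It then fixes four things.

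- The model: "To study the causality between efficacy and treatment prolongation, a multivariate logistic regression will be constructed".
- The entry rule, applied after a univariate regression for each candidate: "Those variables whose statistical significance has a *P* value of <.20 will become part of a multivariate model".
- The final choice: "The model that best explains causality will be determined using a measure of relative statistical model quality, the Akaike information criterion".
- The measure: "The risk measure to be calculated is the relative risk with its 95% CI".

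No covariate is named in advance, nothing says that arm is exempt from the screen or from the AIC step, and no method links the logistic model to the relative risk. The Safety Analysis section applies the same P<.20 screen to the relation between treatment prolongation and absence of adverse events; AIC is mentioned only for efficacy. The abstract describes a univariate analysis of differences between the three groups for each outcome, followed by a multivariate model.

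**The concern.** The trial randomises 1:1:1 to show superiority, so the causal contrast between durations comes from allocation. A search for the best-fitting set of variables adds nothing to that contrast. It does let the outcome data decide what the estimate is adjusted for. An adjusted odds ratio changes with the covariates in the model even when they are perfectly balanced, so two analysts who follow the text with different candidate lists can report different treatment effects.

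Two further points follow from the wording. If arm counts as one of the candidates, a trial in which it fails the screen ends without an adjusted treatment effect or interval. And logistic regression estimates odds ratios; with abstinence expected at 30–50%, an odds ratio is far from a relative risk, so the route from one to the other has to be stated.

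These are methods the article prescribes, not details it leaves open. A later analysis plan would either inherit them or contradict the protocol.

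**Working it through.** **Inputs** (Sample Size Determination section): 30% at 25 days ("the efficacy of cytisinicline prescribed in accordance with the data sheet is 30" per cent); 45% at 50 days in the text but .40 in the bracket beside it; 50% at 75 days; 110 per arm before losses; 80% power; α = .05.

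**1. Reproducing the plan's figure.** The test is not stated. A three-group chi-square test with 2 degrees of freedom has noncentrality λ = n·Σ(pᵢ − p̄)² / [p̄(1 − p̄)], with n per arm.

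- 30/45/50%: p̄ = .4167, Σ(pᵢ − p̄)² = .02167, p̄(1 − p̄) = .2431, so λ = 110 × .02167/.2431 = 9.81. Power is .807, and the smallest n reaching 80% is 109.
- 30/40/50%: p̄ = .40, Σ(pᵢ − p̄)² = .0200, p̄(1 − p̄) = .24, so λ = 110 × .0200/.24 = 9.17. Power is .779, and n = 116 is needed.

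The 110 per arm therefore matches an omnibus comparison at 30/45/50%, and the same λ can be used below.

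**2. Chance that arm fails P<.20 if it is screened.** The 2-df critical value at .20 is −2·ln(.20) = 3.219. The probability that a noncentral chi-square (2 df, λ) falls below it is:

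| Rates | λ (110 per arm) | P(arm fails screen) |
|---|---|---|
| 30/45/50% | 9.81 | 6.0% |
| 30/40/50% | 9.17 | 7.3% |

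With all 134 randomised per arm (402/3) analysed at the same rates, λ is 9.81 × 134/110 = 11.95 and 9.17 × 134/110 = 11.17, and the probabilities fall to 3.1% and 4.0%.

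**3. Odds ratio against relative risk on the planned rates.** RR = p₁/p₀; OR = [p₁/(1 − p₁)]/[p₀/(1 − p₀)].

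| Comparison | RR | OR | OR/RR |
|---|---|---|---|
| 30 v 45% | .45/.30 = 1.50 | (.45/.55)/(.30/.70) = 1.91 | 1.27 |
| 30 v 40% (bracketed value) | .40/.30 = 1.33 | (.40/.60)/(.30/.70) = 1.56 | 1.17 |
| 30 v 50% | .50/.30 = 1.67 | (.50/.50)/(.30/.70) = 2.33 | 1.40 |

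Read as a relative risk on a 30% base, 2.33 would imply .30 × 2.33 = 70% abstinence instead of 50%.

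**4. Does the selection inflate type I error when arm is kept?** This was simulated with P<.20 screening, then backward AIC, arm forced in and no true difference. The assumed set-up was 110 per arm and ten covariates, four of them prognostic with a logit coefficient of 0.35 each. Rejection rates for the two contrasts at .05 were 4.7% and 3.5% in 600 simulated trials (Monte Carlo standard error about 0.9 points), and 5.2% and 5.4% in 3,000 (about 0.4 points). Both are near nominal.

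**The case against.** The strongest reply is that the model is built to study treatment prolongation, so arm is the exposure of interest and the candidate variables are naturally read as covariates. That is fair. The text is silent on arm; it does not say that arm is screened, and the 6–7% applies only if it is. What stands is that retention of the main term should not rest on a reader's charity.

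Several stronger readings are tempting, and the documents do not support them.

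- **Invalid P values and intervals.** A reader might infer a loss of error control from the selection. The simulations do not show it for the type I error of the treatment contrasts when arm is kept. The harm is lack of prespecification.
- **Relative risk as the wrong measure.** It is a legitimate target and can be obtained from a logistic model by standardisation. The article nowhere says that an exponentiated coefficient will be labelled a relative risk, so the gaps in step 3 show what would happen if it were.
- **Inflated number needed or cost ratios.** No section feeds an odds ratio into either. The economic section works from costs, quality-adjusted life years, life-years and an efficacy rate.
- **Conflicting entry rules.** The abstract says "Statistically significant variables will be included in a multivariate model", and the Safety Analysis section says "statistically significant values will be considered those whose *P* value is <.05", which could suggest entry at .05. But the Efficacy Analysis section itself uses the language of significance with the .20 cut, so the abstract is more plausibly a loose summary.
- **Frequent loss of arm.** A much higher failure rate needs smaller true effects than the plan assumes, and the documents give no such rates.

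It is also true that the unadjusted comparison is already signalled in the abstract, and that a trial with arm at P≥.20 would not show superiority on the unadjusted omnibus test. What is lost there is mainly the adjusted estimate and its interval.

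**Conclusion.** The concern holds as a fault of specification. The adjusted model for the main objective is chosen from outcome data, arm is not stated to be protected, and the relative risk has no stated derivation. The dependence of the adjusted estimate on covariate selection follows from the text alone.

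The other two consequences are conditional. Loss of the adjusted estimate in about 6–7% of trials assumes that arm is screened by a 2-df test, the planned rates hold and 110 per arm are analysed; it is about 3–4% with all 134. Overstatement by 27% (17% with the bracketed .40) for the 50-day arm and 40% for the 75-day arm assumes that an odds ratio is reported under the name of relative risk. The finding does not affect the sample size of 402. It should be corrected, but it does not invalidate the design.

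**What to change.** Rewrite the efficacy paragraph so that the primary analysis is one prespecified model that always contains treatment arm and a short list of baseline predictors already collected, for example Fagerström score and cigarettes per day. Site is optional, since randomisation is not stratified by site. Obtain the relative risk and risk difference with 95% CIs by marginal standardisation from the logistic model, or by modified Poisson regression with robust standard errors, and name the method. Report the unadjusted comparison alongside.

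Confine the P<.20 and AIC search to the exploratory analysis of predictors of abstinence and relapse that the efficacy outcomes section already lists. Drop the P<.20 screen from the treatment comparison for safety in the same way.

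The cost is wording only: no new data and no change in sample size. The downside is that the covariate list must be agreed before outcome data are seen. The Results section reports that preselected patients had not yet had their initial visit at the time of writing, so that was still possible then.

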### Safety Analysis

The frequency and percentage of occurrence of adverse reactions shall be determined and categorized according to type/intensity. Calculate whether there are differences in each group compared to what is expected according to the product label.

To examine differences in the data between groups defined by the presence/absence of adverse events, the chi-square test will be applied for qualitative variables and the *t* test or the Mann-Whitney *U* test for quantitative variables. Finally, the causal relationship between safety, defined by the absence of adverse events, and treatment prolongation will be verified using multivariate logistic regression. To determine candidate variables, those with a statistical significance of *P*<.20 will be tested and included in a multivariate model.

All analyses will be performed with the statistical package SPSS (version 19.0; IBM Corp), and statistically significant values will be considered those whose *P* value is <.05.

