## Introduction

### Background

Cytisine (natural alkaloid), also called cytisinicline (marketed form), is extracted from a golden rain tree (*Cytisus Laburnum*) and has adverse effects similar to those reported for nicotine [1,2]. It is a partial agonist of the α4 β2 nicotinic receptors, which, when stimulated, lead to a moderate release of dopamine, contributing to the control of withdrawal symptoms. On the other hand, its antagonistic action blocks the receptor, preventing nicotine from binding to it, thus reducing the reward produced by smoking [1-4]. This duality makes cytisinicline a drug of choice for the treatment of smoking. Current scientific evidence has shown it to be a safe and effective smoking cessation molecule [5].

According to the data sheet [6] the adverse effects attributable to the use of cytisinicline, at standard doses, are mild and infrequent (<20%), with the most frequent (<20%) being gastrointestinal, dry mouth, nausea, dyspepsia, and abdominal pain. Cytisinicline is marketed as an over-the-counter drug in other European countries such as Poland, where it has been used by more than 7 million smokers, and pharmacovigilance data over the more than 50 years it has been on the market have not identified any serious or life-threatening adverse effects in smokers [7-17].

West et al [10] demonstrated that cytisinicline triples the chances of smoking cessation, and in 2 meta-analyses [11,12], where more than 4000 individuals were studied, a relative risk of 1.59 (95% CI 1.43-1.75) and 1.74 (95% CI 1.38-2.19) was found compared to placebo. These data are corroborated by new meta-analyses and systematic reviews [13-15].

In trials where it was compared with other drugs, cytisinicline demonstrated greater efficacy, measured in time to first relapse, compared with nicotine patch monotherapy [18]. Courtney et al [19], in a noninferiority trial, demonstrated that point abstinence at 4 weeks was 42.5% in the cytisinicline group vs 32.3% for varenicline, although noninferiority of cytisinicline vs varenicline could not be demonstrated at 6 months.

In Spain, cytisinicline is introduced as a smoking cessation drug in 2022 and starts to be funded by the National Health System in early 2023. The drug has demonstrated a high level of patient satisfaction and tolerability [20].

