In many countries, cytisinicline is prescribed as a single 25-day course. Studies to date show that the current 25-day cytisinicline regimen is better tolerated and has fewer side effects [20]. However, there is a patient profile in whom this 25-day cytisinicline regimen is not sufficient to control cravings and withdrawal symptoms, increasing the likelihood of relapse, reducing the chances of quitting smoking, and discouraging these smokers from making another serious quit attempt with an effective drug. Recent data from Spain on experience in routine clinical practice with a 25-day cytisinicline regimen show a high rate of relapse after completing treatment. Twenty percent of smokers treated with cytisinicline at this regimen resume smoking from the end of treatment until 2 months after follow-up [25]. Establishing an optimization strategy based on prolonging treatment could increase the drug’s efficacy without being associated with a greater number of side effects, generating a favorable economic impact by increasing the number of smokers who permanently quit. We hypothesize that there is a correlation between increasing the duration of cytisinicline and its efficacy, without being associated with a greater number of adverse events/side effects.

Therefore, we aim to compare the efficacy, safety, and economic impact of this treatment regimen used in routine clinical practice in Spain versus 2 proposed extended treatment regimens (double and triple duration). Different drugs are not compared, but rather 3 different treatment regimens (25, 50, and 75 days) of the same drug (cytisinicline), one of which is the treatment regimen used in daily clinical practice.

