## Discussion

### Principal Findings

Extended treatment regimens with cytisinicline of 50 and 75 days may be more effective than the 25-day treatment regimen currently used in clinical practice. Furthermore, the percentage of adverse effects and the economic cost should not be higher with extended treatment regimens. These expected results will confirm the current scientific evidence on this drug. For example, a multicenter observational study conducted in Spain with more than 300 patients treated with cytisinicline for 25 days shows a relapse rate of 20% in the 2 months following the end of treatment. For every point increase in craving at the end of treatment, the success rate of smoking cessation decreases by 13% at 6 months of follow-up [25]. In other words, the intensity of craving at 4 weeks is inversely correlated with the drug’s efficacy. Increasing the number of days of drug administration could correct this intense desire to smoke.

Two placebo-controlled clinical trials conducted in the United States compared a cytisinicline regimen at a dose of 3 mg every 8 hours for 6 weeks versus 12 weeks. These trials showed an increase in the number of smokers who quit smoking when the treatment regimen was extended beyond 6 weeks. Furthermore, the increased number of treatment days allowed a group of smokers who were gradually reducing their consumption to quit smoking, thus increasing the percentage of smokers who quit. In other words, there will be a group of smokers who will require a longer time to quit smoking [21,22]. No greater number of adverse events were observed with these prolonged regimens. In Europe, a clinical trial in a lung cancer screening program demonstrated that a prolonged cytisinicline regimen with doses different from those specified in the product information—an 84-day regimen—was more effective than the 40-day regimen, without a greater number of side effects [23].

As strengths, it is the first study to compare 3 different cytisinicline regimens: a standard 25-day regimen used in routine clinical practice approved in the product information versus 2 prolonged treatments of double and triple duration without modifying the dose or frequency of the same, unlike other studies that evaluate a higher dose, a different frequency of administration, or compare cytisinicline with other drugs [21-23].

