### Conclusions

Cytisinicline, when used in a standard regimen, triples the likelihood of smoking cessation, as it is a well-tolerated drug with high adherence. However, the percentage of smokers who quit is less than 50%. Therefore, it is essential to design new administration methods and therapeutic regimens.

An optimization strategy for this drug, such as increasing its duration, enhances its benefits without compromising patient safety, representing a new opportunity for smokers to quit.

Furthermore, this study identifies the population of smokers susceptible to a prolonged treatment regimen with cytisinicline. All of this will lead to a reduction in the number of smokers, decreasing, in the short to medium term, morbidity, mortality, and the direct and indirect costs associated with smoking.

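### The hypothesis that longer treatment brings no more adverse events is tested only for a difference at P<.05, which can refute it but cannot support it; the product-label comparison adds a mismatch of exposure

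*Protocol article*

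**What the plan says.** The Introduction (Background) states the hypothesis that efficacy rises with duration "without being associated with a greater number of adverse events/side effects". The Discussion (Principal Findings) expects that "the percentage of adverse effects and the economic cost should not be higher with extended treatment regimens", and the closing Conclusions say that a longer course "enhances its benefits without compromising patient safety".

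The Safety Analysis section sets out three steps:

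- a comparison of every arm with the label: "Calculate whether there are differences in each group compared to what is expected according to the product label";
- chi-square, t or Mann-Whitney tests between patients with and without adverse events;
- a regression, worded as follows: "the causal relationship between safety, defined by the absence of adverse events, and treatment prolongation will be verified using multivariate logistic regression".

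All analyses use P<.05 as the significance criterion. Specific Outcomes (Safety) adds a comparison of adverse-effect percentages between the arms at days 25, 50 and 75 and over the year. The article states no largest acceptable increase and no confidence-interval criterion for safety. The relative risk with 95% CI belongs to the Efficacy Analysis section.

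On the label, Background gives adverse effects as below 20% at standard doses, and the abstract's Methods equate the product-information regimen with 25 days.

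**The concern.** The hypothesis says that something does not increase, while the tools look for a difference. A test of difference supports only one conclusion, that the arms differ. If P exceeds .05, the data may fit no increase and a sizeable increase equally well. Yet that is the result that would match the conclusion the article already anticipates.

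The label comparison raises a separate problem. Arms B and C are treated for two and three times as long as the label regimen. Over the whole course they have more time in which an event can occur, so a percentage above the label could reflect exposure alone. An external rate also cannot answer the trial's own question, which is whether B or C exceeds A.

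At stake is the secondary safety objective. A reassuring statement could rest on low power, and a warning signal could rest on unequal exposure.

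**Working it through.** **Size of the trial.** The document gives no safety sample size, so the arm sizes come from the efficacy calculation in Sample Size Determination. A global three-group chi-square test (2 df, α 0.05, power 0.80) at 30%, 45% and 50% gives 109 per arm, against 110 stated. The total reproduces as 110 × 1.21 = 133.1, rounded up to 134, and 3 × 134 = 402. After a 21% loss, 134 × 0.79 = 105.9, or about 106. The range 106 to 134 therefore runs from all losses to none, and the stated 110 lies inside it.

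**Assumed event rate.** The article gives only an upper bound (below 20%), so 20% and 10% are both shown.

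**Precision.** The half-width of the 95% CI for a difference with equal rates is 1.96 × √(2p(1−p)/n).

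- p = 0.20: 1.96 × √(0.32/134) = 9.6 points; with n = 106, 10.8 points.
- p = 0.10: 1.96 × √(0.18/134) = 7.2 points; with n = 106, 8.1 points.

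Two arms observed at an identical 20% would thus leave an excess of about 10 to 11 points inside the interval.

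**Power of the difference test (two-sided 5%).** Power = Φ[(d − 1.96·SE0)/SE1], where SE0 uses the pooled rate and SE1 the separate rates. For 20% against 30%:

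- n = 134: SE0 = √(2 × 0.25 × 0.75/134) = 0.0529 and SE1 = √((0.16 + 0.21)/134) = 0.0525. The argument is (0.100 − 0.1037)/0.0525 = −0.07, and power is 47%.
- n = 106: SE0 = 0.0595 and SE1 = 0.0591. The argument is −0.28, and power is 39%.

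| Control rate | True rise | n = 106 | n = 134 |
|---|---|---|---|
| 20% | 5 points | 14% | 16% |
| 20% | 10 points | 39% | 47% |
| 20% | 15 points | 69% | 79% |
| 10% | 10 points | 53% | 63% |

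**What supporting the hypothesis would need.** For an assumed margin m (one-sided 0.025, 80% power, equal rates), n per arm = 2p(1−p)(1.96 + 0.84)²/m². At p = 0.20 this is 1005 for 5 points, 252 for 10 and 112 for 15. At p = 0.10 it is 566, 142 and 63. The document names no margin, so these figures show scale only.

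**Label comparison.** Suppose 20% of patients have an event by day 25. The daily hazard is −ln(0.8)/25 = 0.00893.

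- Constant hazard: 1 − 0.8² = 36% by day 50 and 1 − 0.8³ = 49% by day 75.
- Half that hazard after day 25: 1 − 0.8 × 0.8^0.5 = 28% and 1 − 0.8 × 0.8 = 36%.

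These figures illustrate the effect of exposure and do not predict the trial. In them, both extended arms exceed a 20% label figure although the daily risk never rises.

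**The case against.** A reader might infer that the planned tests are useless in both directions. The documents do not support that. The arms are randomised, so a significant excess in B or C would contradict the hypothesis. Under the constant-hazard illustration the test would probably find it: power is 74% to 83% for 20% against 36%, and over 99% for 20% against 49%. Only smaller excesses are likely to be missed.

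A reader might also infer that the plan declares P>.05 to be proof of no increase. It does not. The listed secondary objective is to determine the percentage and number of adverse effects per arm, which is estimation, and the conclusions quoted are anticipatory. A logistic regression would normally yield an estimate with an interval, and how it is presented is often left to an analysis plan. What remains is that the article states both a hypothesis of no increase and the test meant to verify it, and the two do not match. That is a conflict in stated text and not a missing detail.

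On the label, Safety Analysis names neither a rate nor a time window. The link to 25 days is inferred from the abstract and Background, so this part is conditional on whole-treatment rates being used. Day-25 figures are already planned. The illustration also ignores the fall in the daily maximum from 6 tablets to 2, and the Discussion reports no greater number of adverse events with prolonged regimens in earlier trials. These points limit the size of the effect but do not remove the mismatch.

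**Conclusion.** The point holds in a one-sided form: the stated safety tests can refute the hypothesis of no more adverse events but cannot support it. At an assumed 20% rate, a true 10-point rise would be missed 53% to 61% of the time (100 − 47 and 100 − 39). At an assumed 10% rate it would be missed 37% to 47% of the time. The result rests on assumed event rates, on 106 to 134 patients per arm, and on an unadjusted two-arm comparison standing in for the regression.

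The label comparison confounds duration of exposure with excess risk in arms B and C if rates over the whole course are used. It remains a fair comparison over the first 25 days. The matter should be corrected, but it touches a secondary objective and not the primary efficacy result.

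**What to change.** In the Safety Analysis section:

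- Make the main safety result the risk differences B−A and C−A, with 95% CIs, in all treated patients. Give them for patients with any, with moderate or severe, and with serious adverse events.
- State that any claim of no more adverse events will be worded from the upper confidence limit and never from P>.05. Otherwise, describe safety as estimation only and align the hypothesis and the anticipated conclusions with that.
- Limit the label comparison to days 1 to 25, when Table 1 gives all three arms the same regimen and they can be pooled.

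No new patients, visits or measurements are needed. The cost is a more cautious safety claim: with about 10 points of uncertainty either side at a 20% rate, the trial may be able to say only that large increases are unlikely.
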